### Remote patient activity monitoring

Participants were asked to wear the smartwatch daily, including at night, to collect data including daily steps, heart rate, oxygen saturation, and sleep patterns. This information was visible to study coordinators and investigators, as well as MIH paramedics, through the MyDataHelps platform. The data were used to develop automated prompts for participants to provide momentary assessments using CLEAR surveys.

### Virtual comprehensive pulmonary support service

All participants were presented with the option to enroll in a virtual pulmonary care program that provides multimodal support for COPD patients, through a company called Wellinks. The option to enroll in this was made available through the MyDataHelps during the first 90 days of study participation. The program includes coaching to support participant education, treatment adherence, and goal setting, and a virtual pulmonary rehabilitation program that provides a home-based exercise plan including safety instructions and COPD-specific breathing techniques. Additionally, Wellinks participants received a second equipment kit containing a spirometer, pulse oximeter, ten-foot tape measure, exercise band, and an exercise guide. The virtual pulmonary support program team coordinated introductory calls with participants to download their app and configure the spirometer and pulse oximeter devices via Bluetooth which are used to collect additional biometric data. After a comprehensive personalized assessment, a schedule for regular sessions with a health coach was created for participants. All coaching was scheduled and joined through the program’s app, with board-certified health and wellness coaches or nurse practitioners.

In the event of an acute clinical concern, the Wellinks team’s protocol was to instruct participants to contact the MIH clinician or their healthcare provider. The Wellinks team was also empowered to contact the on-duty MIH clinician directly. Participants who enrolled in the Wellinks program were classified as the “full-intervention” group, and those who enrolled in the study but opted not to participate in the Wellinks program were considered the “partial-intervention” group.

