## Analysis plan

Participants are followed longitudinally for 6 months in the pilot study, during which measures of feasibility, clinical efficacy, and operational efficacy will be examined. The feasibility measures observed in the two intervention arms include the response rate for study participants, the adoption rate for virtual pulmonary support, adherence for survey and sensor data, adherence to coaching activities, ability to aggregate sensor data, and ability to measure clinical outcomes through participant-provided data. Table 4 describes planned feasibility outcomes, how they will be operationalized, and the target thresholds indicating feasibility for a larger trial. Figure 3 outlines all data collected during the study.

**Table 4 Tab4:** Feasibility outcomes: A summary of chosen study feasibility outcomes, operationalization of measurement and target thresholds for feasibility

Conceptual outcome	Operational measure	Feasibility benchmark
Recruitment	Rate of enrollment; Number of participants approached, met eligibility and enrolled	• Enrollment of 100 subjects in 12-month study period • Enroll ≥ 20% of invited participants
Retention rate	Number of enrolled participants who remain in the study 6 months	• Participant Retention ≥ 70%
Adoption of virtual pulmonary rehabilitation	Number of participants who opt in to Wellinks	• Participant adoption ≥ 50%
Wearable monitor utilization	Amount of time that participants transmit detectable biometric signals from Fitbit	• Median daily watch use ≥ 17 h • Median watch use ≥ 126 days • Median daily heart rate detection ≥ 1008 min
Completion of study instruments	Number of participants that complete each study instrument	• ≥ 80% of all required study instruments completed by participants
Data abstraction completion	Completeness of required participant clinical data from health records	• ≥ 90% completion of participant clinical data fields

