### All feasibility outcomes will be reported descriptively

Clinical and operational efficacy will be compared across all three groups of COPD participants: full-intervention, partial-intervention, and a control group (no intervention) identified from the EMR using a novel synthetic control study strategy that has been endorsed by the FDA for generating real-world evidence [26, 27]. The clinical efficacy measures include medication requirements, healthcare utilization related to acute or urgent care, total medical expenditure, and, in the intervention arms, participant-reported outcomes (COPD severity, COPD exacerbations, patient activation measure, patient satisfaction, modified Medical Research Council Dyspnea Scale). Lastly, operational efficacy includes time spent during MIH visits, MIH visit escalation to acute care rate, and care management time.

Descriptive analysis will be used to characterize the feasibility outcomes. Continuous measures will be described using mean or median depending on the underlying distribution, and categorical variables will be described as proportions. Associations with sociodemographic characteristics and GOLD classification of COPD severity will be assessed for feasibility outcomes. Count models (Poisson, negative binomial, or zero-inflated negative binomial) will be used to compare healthcare utilization over the course of the study. Continuous models will be used to compare medical expenditure. GEE models with logit or linear link will be used to assess changes over time for COPD severity measurements. Table 5 depicts planned clinical and operational outcomes, operationalization of measurements, and preliminary analysis plans for each outcome.

**Table 5 Tab5:** Clinical and operational outcomes: A summary of chosen clinical outcomes, operationalization of measurement, analysis plan

Conceptual outcome	Operational measure	Analysis plan
Participant perceived COPD severity	• Patient Activation Measure • (Modified Medical Research Council) Dyspnea Scale	All instrument scores will be treated as continuous variables. Regression will be performed using GEE models with logit or linear link. Scores will be compared from participants at baseline and 3 and 6 months
Patient quality of life	• COPD Assessment Test • NIH-PROMIS COPD • Single Item Wellness	
Patient satisfaction	• Patient Satisfaction Measure • Study Exit Survey	

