COPD-related medication changes	• Number of COPD-related medication changes during study period	Outcomes will be treated as count variables. Count models (Poisson, negative binomial, or zero-inflated negative binomial) will compare outcomes between the full-intervention, partial-intervention, and synthetic control
ED utilization	• Number of ED visits during study period	
Hospitalization	• Number of COPD-related hospitalizations during study period	
Medical expenditures	• Total claims costs during study period	Claims will be considered in aggregate for all costs paid during the study period; they will be treated as a continuous variable. Continuous models will compare outcomes between the full-intervention, partial-intervention, and synthetic control
COPD-related MIH effort	• Number of MIH visits completed • Median MIH Visit time • Median physician effort time per MIH visit	Descriptive

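### Full and partial groups are set by an opt-in open for 90 days, but utilization and costs are counted from study start, so pre-Wellinks time is credited to the full group

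*Protocol article*

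**What the plan says.** The group definition is in the protocol article, Methods, *Virtual comprehensive pulmonary support service*. Of the Wellinks option it says: "The option to enroll in this was made available through the MyDataHelps during the first 90 days of study participation". The section later defines the groups: "Participants who enrolled in the Wellinks program were classified as the “full-intervention” group". Everyone else in the study, having declined the option, counts as partial-intervention. Neither definition uses the opt-in date or a minimum exposure.

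Follow-up is stated in *Analysis plan*: "Participants are followed longitudinally for 6 months in the pilot study". The next subsection plans the group contrast: "Clinical and operational efficacy will be compared across all three groups of COPD participants: full-intervention, partial-intervention, and a control group". In Table 5 the outcome window for medication changes, ED visits, hospitalizations and claims costs is the study period; for ED visits the operational measure reads "Number of ED visits during study period". The count and continuous models "will compare outcomes between the full-intervention, partial-intervention, and synthetic control".

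The article describes no landmark and no time-varying exposure. It gives no rule for events before opt-in, or for participants who leave before opting in.

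**The concern.** A behaviour after baseline decides the group, while outcomes are counted from baseline. This has three consequences.

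- **Misclassified time.** Before opting in, a full participant receives exactly what a partial participant receives. Events and costs in that time are nevertheless credited to the full group, which dilutes any real effect.
- **Selection by withdrawal or death.** A participant who leaves or dies before opting in cannot become full and falls into the partial group.
- **Selection by early events.** If an early exacerbation discourages opt-in, its events stay in the partial group and the full group looks better. If it prompts opt-in, the reverse happens.

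At stake is what the study says Wellinks adds to the app, smartwatch and MIH access. The Discussion presents the pilot as groundwork for a larger study of clinical, operational and cost outcomes with the same synthetic control design, so a distorted full-versus-partial estimate could be carried into its planning.

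**Working it through.** The article gives no event rate, effect size, power or distribution of opt-in times, so there is no planned figure to reproduce.

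**Inputs from the article:** opt-in window, days 0 to 90; follow-up, 6 months, taken as 180 days; retention benchmark, 70%; adoption benchmark, 50%; enrolment target, 100 (all benchmarks from Table 4).

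**Assumed:** the opt-in timing, the event rate, and how events affect opt-in.

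**1. Share of counted time before exposure.** With mean opt-in day m, the share is m/180: 15/180 = 8.3%, 45/180 = 25% (uniform over the window), 90/180 = 50% (everyone on the last day).

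**2. Dilution.** With a constant event rate, complete follow-up and a true post-opt-in rate ratio RR, the fixed-group ratio is [m + (180 − m) × RR]/180. For RR = 0.70:

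| Opt-in timing | Calculation | Apparent ratio |
|---|---|---|
| All at day 0 | (0 + 126)/180 | 0.70 |
| Mean day 15 | (15 + 115.5)/180 | 0.725 |
| Uniform, mean day 45 | (45 + 94.5)/180 | 0.775 |
| All at day 90 | (90 + 63)/180 | 0.85 |

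**3. Withdrawal before opt-in, no true effect.** Assume 50% are willing to opt in, uniform timing, and a constant dropout hazard giving 70% retention. The daily hazard is −ln(0.70)/180 = 0.00198. Over 90 days this is 0.178, so the mean chance of still being in the study at the opt-in day is (1 − e^−0.178)/0.178 = 0.916. The full share is 0.5 × 0.916 = 0.458. Half of the 70% retained are willing, so retention is 0.35/0.458 = 76.4% in full and 0.35/0.542 = about 64.5% in partial. A simulation of 2,000,000 participants gave 76.4% and 64.5%. With everyone opting in at day 0 it gave 70.0% and 69.9%.

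**4. Event-dependent opt-in, no true effect.** The same simulation, with 0.5 events per person per 6 months, gave:

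| Scenario | Fixed-group rate ratio | Time-varying rate ratio |
|---|---|---|
| 70% retention, opt-in unrelated to events | 0.998 | 0.998 |
| Complete follow-up, an early event halves opt-in | 0.807 | 0.998 |
| 70% retention, an early event halves opt-in | 0.798 | 1.004 |

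In the first row, raw counts per participant gave 1.144 if counting stops at dropout; a person-time offset removes that excess.

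**5. A true ratio of 0.70, 70% retention.** The fixed-group rate ratio was 0.782 with opt-in unrelated to events and 0.596 when an early event halves opt-in. Time-varying exposure gave 0.699 and 0.702. Every simulated participant has the same underlying event rate, so these runs test time alignment only and not self-selection.

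**The case against.** Several stronger readings are tempting, and the article does not support them.

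- **That every full-versus-partial contrast is biased.** With a person-time offset, no effect and opt-in unrelated to events, the rate ratio is 1.00. Participant-reported scores in Table 5 are compared mainly over time, and MIH effort is descriptive.
- **That this is chiefly immortal time.** Time before opt-in is strictly immortal only for death and withdrawal. A participant can have an ED visit or admission and opt in afterwards, so for these counts the problem is misclassified exposure and possible event-dependent opt-in.
- **That all early leavers are partial.** Only those who leave before opting in are; someone who joins Wellinks on day 1 and leaves on day 30 is full.
- **That a retention contrast is planned.** Table 4 sets one overall benchmark. The retention gap matters only if retention is shown by group.
- **That raw counts will be inflated.** This requires counting to stop at dropout. The data sources include the EHR and Medicare claims, so it may not.

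Nothing in the article suggests that early events deter opt-in; they could as easily prompt it, a case not simulated. Precision is also low. With 100 participants split evenly and 0.5 events each, both groups have about 25 events, and the 95% interval around a ratio of 1 is exp(±1.96 × √(1/25 + 1/25)), or 0.57 to 1.74. The null biases shown above lie within that interval. No feasibility benchmark depends on the contrast.

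These points lower the severity and rule out a single headline bias. They do not remove the mismatch, which lies in the stated group definition and outcome window and not in detail an article leaves to the full plan.

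**Conclusion.** The point holds for the full-versus-partial comparisons of medication changes, ED visits, hospitalizations and costs. As written, up to 50% of a full participant's counted time can precede Wellinks exposure, or 25% on average under the uniform assumption. A true ratio of 0.70 would appear as 0.725 to 0.85 for mean opt-in days from 15 to 90. If early events or withdrawal affect opt-in, bias in either direction is possible with no true effect; its size depends on opt-in timing and behaviour that the article does not give. If most participants opt in at onboarding, it is small.

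A reader might infer that this must be fixed before the study can be interpreted. That goes too far: the contrast is secondary in a feasibility study of about 100 people whose main outcomes are descriptive. Severity is moderate.

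**What to change.** In the full-versus-partial utilization and cost models, treat Wellinks enrolment as time-varying. Person-days, events and costs before the opt-in date count as partial and those after it as full, with a person-time offset in the count models. A day-90 landmark, counting only later outcomes, can serve as a sensitivity analysis; it discards about half of follow-up, so it should not be the main analysis. Apply the same time alignment to any retention or adherence figures shown by group. Label full-versus-partial as exploratory and self-selected, since time alignment does not change who chooses to opt in.

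The cost is analysis wording and fewer full-intervention person-days. For illustration, take 50 participants per group, complete follow-up, uniform opt-in and 0.5 events per 180 days. Full person-days fall from 50 × 180 = 9,000 to 50 × 135 = 6,750, and partial rise to 11,250. Expected events become 18.75 and 31.25, and the interval around a ratio of 1 is exp(±1.96 × √(1/18.75 + 1/31.25)), or 0.56 to 1.77, against 0.57 to 1.74 before. The change needs each participant's opt-in date. The article does not say that this is recorded, but it should be available because opt-in was offered through the study app.

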### MIH integration

To provide on-demand, field-based clinical support to participants, all enrolled participants were invited to utilize the institution’s affiliate MIH program for the duration of their participation [24]. MIH programs are new models of care that leverage mobile resources, including specially trained paramedic-level clinicians, called community paramedics, to evaluate and care for patients in an out‐of‐hospital environment in coordination with health systems [24, 25]. By providing field-based care, such programs are intended to eliminate barriers that patients encounter in accessing timely management of acute illness. They complement digital and remote clinical interventions by providing flexible, face-to-face evaluation and treatment to patients. During episodes of acute clinical symptoms (such as worsening shortness of breath), participants, their caregivers, and the Wellinks team were empowered to request an MIH visit. The community paramedics are available 24 h a day, 7 days a week, and present to participants’ homes within 2 h of a request. Upon arrival, they evaluate and treat participants, aided by mobile diagnostic tools and medications as well as telehealth support from an on-call supervising physician, then develop a plan of care with the participant, which usually entails treatment in the home and intensive care coordination with the participant’s ambulatory providers. The MIH program is specifically equipped to initiate treatment for COPD exacerbation with inhaled bronchodilators and parenteral antibiotics and steroids. If a participant is too acutely ill to remain at home, the participant is diverted into the emergency services system. To streamline care, the community paramedic team and their supervising physicians had access to participants’ study dashboards so that they could review their aggregated clinical data and recent changes in biometric patterns.

In addition to the education and literature provided during study onboarding, the participant-facing MyDataHelps app contained a “Call MIH” button which enabled the participant to easily contact MIH for an in-home assessment if they felt unwell by directly connecting them with the MIH request line. The MyDataHelps app was set to issue a prompt to the participant to consider calling MIH when pre-set metrics are consistent with a potential COPD exacerbation (Table 3). Finally, research coordinators were instructed to refer participants to the MIH hotline if any clinical concerns were raised while on a phone call with participants. The MIH program did not proactively provide care because of alerts or flags observed from participant-reported data or biometric signals in this pilot phase. Clinical care provided by the MIH paramedics for the study’s participants was identical in practice to the care provided to patients outside the study.

## Analysis plan

Participants are followed longitudinally for 6 months in the pilot study, during which measures of feasibility, clinical efficacy, and operational efficacy will be examined. The feasibility measures observed in the two intervention arms include the response rate for study participants, the adoption rate for virtual pulmonary support, adherence for survey and sensor data, adherence to coaching activities, ability to aggregate sensor data, and ability to measure clinical outcomes through participant-provided data. Table 4 describes planned feasibility outcomes, how they will be operationalized, and the target thresholds indicating feasibility for a larger trial. Figure 3 outlines all data collected during the study.

**Table 4 Tab4:** Feasibility outcomes: A summary of chosen study feasibility outcomes, operationalization of measurement and target thresholds for feasibility

Conceptual outcome	Operational measure	Feasibility benchmark
Recruitment	Rate of enrollment; Number of participants approached, met eligibility and enrolled	• Enrollment of 100 subjects in 12-month study period • Enroll ≥ 20% of invited participants
Retention rate	Number of enrolled participants who remain in the study 6 months	• Participant Retention ≥ 70%
Adoption of virtual pulmonary rehabilitation	Number of participants who opt in to Wellinks	• Participant adoption ≥ 50%
Wearable monitor utilization	Amount of time that participants transmit detectable biometric signals from Fitbit	• Median daily watch use ≥ 17 h • Median watch use ≥ 126 days • Median daily heart rate detection ≥ 1008 min
Completion of study instruments	Number of participants that complete each study instrument	• ≥ 80% of all required study instruments completed by participants
Data abstraction completion	Completeness of required participant clinical data from health records	• ≥ 90% completion of participant clinical data fields

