**Fig. 2 Fig2:**
[figure not shown]
SPIRIT depictionof study activity and outcomes

**Table 1 Tab1:** Healthy at home intervention components: This multimodal intervention included a study app, smartwatch, access to acute care through a mobile integrated health program and virtual pulmonary support services

Intervention component	Description	Interaction with other components	All participants or opt-in
MyDataHelps App (main study app)	Houses all participant-facing forms and questionnaires including screening and consent. Prompts participants to complete scheduled assessments. Receives information from biosensors and is linked to participants’ EHR and claims data to aggregate all data streams. Generates momentary assessments triggered by participant responses or biometric data	All participant-level MyDataHelps data is visible to the Wellinks and MIH team on the study dashboard. Clinical data can trigger alert to participants through the app suggesting a home assessment from the MIH team and connect participants directly with the MIH visit request line	All
Fitbit Smartwatch	Collects biometric data. All data is visible to participants, study team, MIH clinicians, and Wellinks coaches through the MyDataHelps	Biometric patterns trigger alert to patients suggesting MIH visits. Biometric data is visible to clinical and research teams	All
Mobile Integrated Health Program (community paramedics and MIH physicians)	Community paramedics are available on-demand to perform home visits to evaluate and treat participants experiencing acute symptoms with support from a supervising physician. The program is specifically equipped to initiate treatment for COPD exacerbation	MIH team can view participant-level data in MyDataHelps. MIH visits offered to participants reporting worsening symptoms or exhibiting concerning biometric data through the study app. Research and Wellinks team refer participants to MIH team for all acute clinical concerns	All
Wellinks Virtual Pulmonary Rehabilitation Program	Coaching program to support participant education, treatment adherence, and goal setting, as well as a virtual pulmonary rehabilitation. Hosted on a separate program-specific app	Wellinks team can view participant-level data in MyDataHelps to support coaching plans. Wellinks can contact MIH team with any acute concerns requiring clinical evaluation	Opt-In

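### The data-abstraction benchmark in Table 4 cannot register missed events: for the count outcomes, a complete field may still hold too low a number

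*Protocol article*

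**What the plan says.** The Analysis plan introduces Table 4 as giving "the target thresholds indicating feasibility for a larger trial". Its last row, on data abstraction, is measured as "Completeness of required participant clinical data from health records" and is met at "≥ 90% completion of participant clinical data fields". The list of required fields is not given.

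Table 5 defines the utilization and treatment outcomes as counts: "Number of ED visits during study period", "Number of COPD-related hospitalizations during study period" and "Number of COPD-related medication changes during study period". It names no data source for them.

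On sources, Table 1 says that the study app "is linked to participants’ EHR and claims data to aggregate all data streams". The Fig. 3 caption lists the Epic health record and Medicare claims among the sources. Setting and participants requires that a person receive care through the hospital system, but not that all care is received there. The Discussion says that enrollment does not depend on type of insurance.

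The Analysis plan also names "ability to measure clinical outcomes through participant-provided data" as a feasibility measure. A separate Table 4 row sets an 80% benchmark for completion of the study instruments.

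**The concern.** A feasibility threshold should be able to give the wrong answer's opposite: it should fail when the thing it guards against happens. The risk in abstracting utilization from health records is less that a cell is left empty than that a visit to another hospital never reaches the record. For a count, such a visit leaves no gap. The field reads 0, or one fewer than the truth, and is scored as complete.

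The article leaves room for this. Care outside the system is not excluded, one health record is named, and Medicare claims need not exist for every participant in a cohort with any insurance. No passage compares counts between sources or sets a threshold for capture.

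The Discussion says the pilot is meant to show that a larger synthetic-control study of clinical, operational and cost outcomes is feasible, and the controls are to be identified from the EMR. Data abstraction could be declared feasible for that design without any evidence on how many ED visits and admissions the record sees.

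**Working it through.** The 90% figure is a set threshold with no derivation, so there is nothing to reproduce. The question is whether the score depends on capture.

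**Inputs from the article:** benchmark 90%; count outcomes from Table 5; planned enrollment of 100 (Table 4).

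**Assumptions (not in the article):** true 6-month visits follow a negative binomial distribution with mean m = 0.5, 1 or 2 and dispersion 1; each visit is captured with probability c; a count with no recorded event is entered as 0; the number of required fields is 4 to 20; 20% to 60% of participants have no Medicare claims.

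**Step 1. Completion against capture.** Completion of a count field is the share of non-blank entries. With 0 entered when nothing is found, that share is 1 whatever c is. The observed visit rate is c × m. The share of participants with at least one missed visit is (1 − c)m / [1 + (1 − c)m]. Simulation with 100 participants agrees with both formulas.

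| Capture c | Count fields complete | Observed / true visits | Participants undercounted, m = 0.5 / 1 / 2 |
|---|---|---|---|
| 100% | 100% | 1.00 | 0% / 0% / 0% |
| 80% | 100% | 0.80 | 9% / 17% / 29% |
| 60% | 100% | 0.60 | 17% / 29% / 44% |
| 40% | 100% | 0.40 | 23% / 38% / 55% |
| 0% | 100% | 0 | 33% / 50% / 67% |

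For example, at c = 60% and m = 0.5: 0.4 × 0.5 = 0.2, and 0.2 / 1.2 = 17%. The completion column does not move.

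**Step 2. Effect on the overall score.** If a share f of the required fields are always-filled counts, the other fields need completion of (0.9 − f)/(1 − f) to reach 90% overall:
- f = 50%: 0.4 / 0.5 = 80%
- f = 75%: 0.15 / 0.25 = 60%
- f = 90%: 0 / 0.1 = 0%

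So the benchmark can still fail, but only through the fields that can be blank, and less easily as the share of counts grows.

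**Step 3. Does a claims field make the score sensitive?** Suppose one of k required fields comes from claims and is blank for a share u of participants. Overall completion is then 1 − u/k if all else is filled. With k = 10 and u = 20% to 60% it is 98% to 94%, a pass. With u = 60% it is 88% at k = 5 and 85% at k = 4, a fail. Even then the score reacts to missing insurance data, not to missed visits.

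**The case against.** The strongest defense is that the row does what its title says. It is about abstraction completeness, it is measured as completeness, and its threshold is on completeness. It makes no claim about event ascertainment. The list of required fields, the coding of zero against missing and the handling of outside care may sit in the full protocol. This stands in part: the row is internally consistent, and entry of 0 is an inference from usual practice. But the article itself fixes the measure and makes it a threshold for a larger trial, and no other Table 4 row tests capture of the Table 5 counts.

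A reader might infer that Table 4 fails to test the measure based on participant-provided data that the Analysis plan names. The documents do not support that. The section on clinical efficacy lists participant-reported outcomes in the intervention arms, and the instrument-completion row plausibly serves them.

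A reader might also infer that the benchmark will be met whatever happens. It will not: Steps 2 and 3 show how it can fail.

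Nor does the article show that a large share of visits is missed. It gives no out-of-system share and no visit rate, and it does not say that ED visits and admissions come from the EHR alone. Linked claims could recover some outside visits. They are limited by who has Medicare, and the benchmark makes no use of them.

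Finally, if capture were equal in intervention and control groups, a ratio of rates would be unaffected, since c cancels. Absolute rates would still be too low, and equal capture is itself something the plan does not check.

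**Conclusion.** The point holds in a limited form. For ED visits, COPD-related hospitalizations and medication changes, the result of the data-abstraction benchmark does not depend on whether the events were found. Completion stays at 100% across the whole range of capture, while the observed count falls in direct proportion to capture. This rests on one unstated convention, that a count with no recorded event is entered as 0.

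The size of any actual undercount cannot be determined from the article. The percentages in the table illustrate the mechanism under assumed visit rates and do not estimate what happens in this cohort. The row remains useful as a data-quality check on fields that can be blank. It should not be read as evidence that the utilization outcomes of a larger trial can be measured.

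**What to change.** In the data-abstraction row of Table 4:

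1. Keep the 90% completion benchmark, restricted to fields that can be blank.
2. Add an event-capture measure for ED visits and hospitalizations. Among participants with linked Medicare claims, report the share of claims-identified events over the 6 months that are also found in the EHR, with a target (for example at least 90%). Give numerator and denominator.
3. Report the number of participants without claims as not assessable. They should not enter the denominator through the EHR alone, because EHR capture would then be 100% by construction.
4. Use participant report as a second comparator only if an existing instrument records acute-care visits. None in Table 2 is described as doing so; otherwise a new item would be needed.
5. State how a count with no recorded event is entered.

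The cost is a little cross-matching of data the study already plans to link. The figure will cover only the Medicare-linked subset, does not address medication changes, and will probably look less favorable than field completion. It may also be imprecise. With 100 enrolled, 40% to 80% with claims and a mean of 0.5 to 2 visits (assumed), the denominator would be between 100 × 0.4 × 0.5 = 20 and 100 × 0.8 × 2 = 160 visits. At 20, each missed visit moves the result by 5 percentage points, so the target should be read with an interval.
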